At present, more than 50 smoking-cessation apps for smart phones are available to download. However, very few have evidence-based content [19]. Also, most apps need to be actively opened by the person. So, it is important not only to download the app but also to use it as intended [19]. This contrasts with SMS-based interventions where the person automatically receives a message with information or another intervention component and does not have to actively decide to continue accessing the intervention. This increases the potential for high levels of exposure and strong adherence to intervention content in real time in everyday settings.

Research on mobile phone-based interventions for smoking cessation has so far been very scarce. One of the first studies of a solely SMS-based intervention was performed in New Zealand in 2005 - the ‘Do u smoke after txt?’ study. The study showed a significant 6-week increased quit rate in the SMS group compared to the control group (28% versus 13%), whereas at 6 months the results were difficult to interpret due to missing values [18]. A later study, the ‘txt2Stop’ study from the UK, was based upon a modified version of the New Zealand intervention. Its pilot study showed at 6 months follow-up a self-reported quit rate of 26% in the intervention group compared with 12% in the control group [17], and in the main study the quit rate was 19.8% in the SMS intervention group compared to 13.5% in the control group. The biochemically verified abstinence rate was 10.7% in the SMS group and 4.9% in the control group [15].

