### Objectives and hypotheses

The objective of the study is to evaluate the effectiveness of a SMS-based smoking cessation intervention. Participants in both the intervention and control group are told that they are free to seek any other treatment they want during the trial in the same manner as in previous studies [15-18].

Six hypotheses in total are being tested. The 2 primary hypotheses are that a greater proportion of participants in the intervention group than in the control group will report: 1) prolonged abstinence (8 weeks) and 2) recent abstinence (4 weeks) at follow-up. Secondary hypotheses are that the intervention group compared with the control group will report: 3) greater proportions of current abstinence (1 week); 4) a higher number of quit attempts; 5) greater use of other smoking cessation services; and 6) smoking fewer cigarettes among those still smoking at follow-up.

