### Randomisation and other study procedures

Smokers who respond to the invitation Email and want more information about the study will be referred to a page with more information about the study emphasising that only students who are daily or weekly smokers willing to set a stop date within a month are eligible for the study. Most previous SMS-based smoking cessation studies have used the inclusion criteria - willing to set a stop date with 2 to 4 weeks - facilitating recruitment of a more engaged population both in the intervention and control group and thereby avoiding a larger drop-out of randomised participants before the specified quit date [15,18,23].

By emphasising that participants should be willing to set a stop date this would prevent randomised participants dropping out of the study before completing the intervention. After having read the information about the study all participants gave informed consent to participate by clicking on a link. After informed consent was obtained the participants were guided to a baseline assessment page. The hyperlink contained within the body of the Email is no longer valid after completion of the questionnaire when the responses are stored in the study database. This prevents multiple responses, while allowing the questionnaire to be completed in more than one session if required. After completion of the baseline assessment the students will be asked to provide their telephone number. Then they will immediately receive a SMS that will have to be responded to by writing, ‘start’, in order to confirm that they had stated the right telephone number.

Participants will immediately be randomised to an intervention or waiting list (control) group. Each participant is allocated a number 1 or 2 with equal probabilities using Java’s built in random number generator (java.util.Random). Randomisation is thus fully computerised, does not employ any strata or blocks, and is not possible to subvert, as this and all subsequent study processes are fully automated.

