### Sample size

Based upon previous studies, we expected an absolute difference in cessation rates between the intervention and control group of 5% (with 10% quitting in the intervention group and 5% in the control group) [15,20].

To achieve 80% power with a significance level of 0.05 (2-sided) and correction for continuity, a sample size of 474 persons is needed in each group. If there is 30% attrition in the follow-up measurement the number needed in each group is 677, with the total required sample size being 1,354. The allowance for attrition is deliberately conservative.

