*Secondary outcome measures*:Self-reported 7-day point prevalence of smoking abstinence (defined as not smoking any cigarettes in the past 7 days).Mean number of quit attempts since taking part in the study.Number of uses of other smoking cessation services (prescribed medication, nicotine replacement medication, counselling, calling the help-line or any other help) since first invitation to the study.Numbers of cigarettes smoked weekly (for participants still smoking at the time of follow-up only.

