#### Primary analyses

The primary analyses will assume that missing outcome data are missing at random and, therefore, will be performed on complete cases only.

The binary outcomes of self-reported prolonged abstinence, 4-week prevalence of smoking abstinence and 7-day point prevalence of smoking abstinence will be analysed by logistic regression and results presented as odds ratio (95% CI). Number of quit attempts and number of uses of other smoking cessation services will be analysed by negative binomial regression and results presented as ratio of means (95% CI). Numbers of cigarettes smoked weekly will be analysed by logarithmic transformation and linear regression and results presented as ratio of geometric means (95% CI).

All regression analyses will be adjusted for by the following baseline variables: gender, years of smoking, average number of cigarettes smoked weekly, severity of dependence as measured by Fagerström’s Nicotine Dependence Scale and amount of ‘*snus*’ used at baseline.

Effect modification analyses will be performed for the two primary outcomes and the following potential effect modifiers measured at baseline: gender, average number of cigarettes smoked weekly, amount of ‘*snus*’ used weekly, and severity of dependence as measured by Fagerström’s Nicotine Dependence Scale. Each effect modification will be assessed by adding the appropriate interaction term to the adjusted regression model. Consideration for adjustment for multiplicity of comparisons will be discussed. All tests will be performed 2-sided with a 5% level of significance.

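### Hypothesis 6 compares weekly cigarettes only among continuing smokers, a subset the intervention is expected to change, so it is not a randomised comparison and may be biased in either direction

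*Protocol article*

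**What the plan says.** Under Objectives and hypotheses, the last of six hypotheses to be tested is that the intervention group will report "smoking fewer cigarettes among those still smoking at follow-up". Outcome evaluation defines the matching secondary outcome as "Numbers of cigarettes smoked weekly (for participants still smoking at the time of follow-up only". Primary analyses gives the model: "Numbers of cigarettes smoked weekly will be analysed by logarithmic transformation and linear regression". The result is a ratio of geometric means with a 95% CI, adjusted for gender, years of smoking, baseline weekly cigarettes, Fagerström score and snus, and tested two-sided at 5%.

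Two other statements bear on this. Sample size expects quitting to differ between the arms, "with 10% quitting in the intervention group and 5% in the control group". The opening of Data analysis, invoking intention to treat, commits every analysis to everyone who supplied follow-up data, kept in the arm to which they were allocated. The article does not label the smokers-only comparison as descriptive or non-randomised, and it names no version that includes abstainers.

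**The concern.** Still smoking at follow-up is essentially the complement of what hypotheses 1 to 3 say the intervention will change. Restricting to it selects participants on an outcome, and selects differently in the two arms. If the extra quitters in the intervention arm are lighter smokers, its remaining smokers are heavier on average, and the intervention can look worse, or a real reduction can be hidden. If the extra quitters are heavier smokers, the intervention can look as if it helped people cut down when it did not. Either way, a difference can arise with no effect on anyone's consumption.

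The restriction also cannot be squared with the Data analysis commitment. Abstainers who returned the questionnaire have follow-up data but are left out because of what they reported. The planned sensitivity analyses do not reach this problem. The informatively missing odds ratio and the repeated-attempts model concern missing abstinence data, not selection into the smoker subset.

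**Working it through.** **1. The plan's own figure.** Sample size states, per arm: "To achieve 80% power with a significance level of 0.05 (2-sided) and correction for continuity, a sample size of 474 persons is needed in each". With p1 = 0.10, p0 = 0.05, mean 0.075 and d = 0.05:

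- Uncorrected n = [1.960 × √(2 × 0.075 × 0.925) + 0.842 × √(0.10 × 0.90 + 0.05 × 0.95)]² / 0.05² = 434.4, that is 435.
- With continuity correction, n = (434.4/4) × [1 + √(1 + 4/(434.4 × 0.05))]² = 473.6, that is 474. This reproduces the plan.
- Attrition: 474/0.70 = 677.1, against the stated 677 and total of 1,354.

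So 474 followed up per arm is a fair basis for what follows.

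**2. Who is compared.** At 10% and 5% quitting, 474 × 0.90 = 427 smokers remain in the intervention arm and 474 × 0.95 = 450 in the control arm. The share of control smokers with no counterpart in the intervention arm is (0.10 − 0.05)/(1 − 0.05) = 5.3%.

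**3. Unadjusted worst cases.** These need an SD for log weekly cigarettes, which the article does not give. I assume 0.9 and a normal distribution.

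- *All quitters in both arms are the lightest smokers.* The mean shift in an arm with quit share q is φ(z_q)/(1 − q), which is 0.195 at 10% and 0.109 at 5%. The spurious ratio is exp[0.9 × (0.195 − 0.109)] = 1.08. For the quit rates the Background reports for a similar trial ("the quit rate was 19.8% in the SMS intervention group compared to 13.5% in the control group") the same formula gives 1.09.
- *Only the extra quitters are the lightest.* Trimming 5.3% shifts the mean by 0.113 SD, so the ratio is exp(0.9 × 0.113) = 1.11. If they are instead the heaviest, it is 1/1.11 = 0.90.

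These are bounds without the planned adjustment, not expected values.

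**4. Simulation with the planned kind of adjustment.** Assumptions: 474 per arm, no treatment effect on cigarettes in anyone, log-SD 0.8, baseline to follow-up correlation 0.6. The log-odds of quitting fall by g per SD of baseline consumption and by g per SD of an unmeasured heaviness factor. There were 2,000 runs per row, and the model adjusts for baseline consumption.

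| Quitting | g | Adjusted ratio | Rejection at nominal 5% |
|---|---|---|---|
| 10% v 5% | 0 | 1.00 | 5.6% |
| 10% v 5% | 0.5 | 1.016 | 6.5% |
| 10% v 5% | 1.0 | 1.026 | 9.2% |
| 10% v 5% | 1.5 | 1.031 | 11.7% |
| 19.8% v 13.5% | 0 | 1.00 | 5.3% |
| 19.8% v 13.5% | 0.5 | 1.020 | 8.3% |
| 19.8% v 13.5% | 1.0 | 1.031 | 10.6% |
| 19.8% v 13.5% | 1.5 | 1.041 | 15.2% |

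Without adjustment, the 10% v 5% rows with g above 0 give ratios of 1.026 to 1.053 and rejection of 8.3% to 17.3%, so adjustment helps but does not remove the bias. At log-SD 0.9 the log ratio scales by 0.9/0.8, so 1.041 becomes about 1.046. A smaller simulation at 0.9 (300 runs per setting) gave 1.019 to 1.047 and rejection of 7.7% to 12.7%.

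**5. Direction.** The assumed distributions are symmetric, so if heavier smokers quit more readily the ratios invert: 1.02 to 1.05 becomes about 0.98 to 0.95.

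**The case against.** The case for leaving the plan alone has real content.

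- *The adjustment covers much of the selection.* Baseline cigarettes, Fagerström score and years of smoking are obvious drivers of who quits. This stands, and it is why the adjusted figures are small. It does not reach unmeasured factors, or the importance of quitting, which is collected at baseline but not adjusted for.
- *No bias is demonstrated.* The article gives no SD, no correlation and no link between heaviness and quitting. This also stands: with g = 0 the ratio is 1.00 and the test holds its level. A reader might infer that the test is certainly biased against the intervention, but the documents fix neither the presence nor the direction of bias.
- *There may be no conflict with the intention-to-treat statement.* It could be read as covering those with data on the outcome in question, which abstainers lack by definition. But they lack it because of their result, not through non-response, so the two sections still need reconciling.
- *Hypothesis 6 asks a legitimate question about cutting down.* It does, and including abstainers answers a different one. Reporting the smokers-only figure openly as non-randomised respects that interest; a confirmatory-style test does not.

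A reader might also infer that the log transformation fails on zeros because weekly smokers are eligible. The documents do not support this. Eligibility excludes people who do not smoke every week, the outcome is confined to continuing smokers, and no recall week is defined that could contain a zero.

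**Conclusion.** The concern holds in a limited form. As specified, hypothesis 6 is a tested comparison within a post-randomisation subset that the trial expects its intervention to alter, and it conflicts with the stated analysis population. That much follows from the article alone.

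The size rests on assumptions outside it: log-SD 0.8 to 0.9, correlation 0.6, and quitting that depends on measured and unmeasured heaviness. On those, the adjusted spurious ratio is about 1.02 to 1.05 where lighter smokers quit more, with rejection of about 7% to 13% (15% in the most extreme setting shown). The low end of that range is barely distinguishable from 5%: the 7.7% from 300 runs has a 95% interval of about 5.2% to 11.2%. The ratios of 1.08 to 1.11 are unadjusted worst cases and should not be quoted as the expected bias.

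A reader might take this as undermining the trial's main result. It does not: this is one of four secondary outcomes, and the primary outcomes and the sample size are untouched.

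**What to change.** - Make the tested comparison weekly cigarettes among all participants who complete the questionnaire containing the cigarette item, in the arm allocated, with abstainers counted as 0. Use a model that allows zeros, such as the negative binomial regression already planned for the other counts, with the same covariates.
- Treat those who answered only the two SMS questions on the primary outcomes as missing on this outcome, whether abstinent or smoking. Scoring only the abstainers among them as 0 would add quitters while dropping smokers, so missingness would depend on the result. The same rule should apply to anyone reached by telephone who is not asked the cigarette item; the article does not say what the calls cover.
- Keep the smokers-only ratio of geometric means as a descriptive figure, labelled non-randomised and without a hypothesis test.
- Reword hypothesis 6 and the outcome definition to match, which also brings them into line with the Data analysis section.

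The cost is wording; no new data are needed. The drawback is that the estimate combines quitting with cutting down. With no effect on consumption and quitting unrelated to it, 10% against 5% quitting alone gives a ratio of means of 0.90/0.95 = 0.95. The outcome therefore partly overlaps the abstinence outcomes and should be interpreted alongside them.

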### Data analysis

The data analysis will conform to the pre-specified statistical analysis plan described below. The analysis will start after collection of the follow-up data. There will be no interim analyses or stopping rules. Following the intention-to-treat analysis strategy, all analyses will include all participants with follow-up data in their groups as randomised, and sensitivity analyses will include all randomised participants to explore different assumptions about the missing data [37].

#### Descriptive analysis

A flowchart of recruitment of participants is displayed in Figure 1. The number of screened students who fulfil the study inclusion criteria, and the number included in the primary and secondary analyses as well the reason for exclusion from these analyses, will be reported. Summary tables (descriptive statistics and/or frequency tables) will be provided for baseline and follow-up variables, as appropriate. Continuous variables will be summarised with descriptive statistics (n, mean, standard deviation for data with normal distribution, or median and interquartile range for non-normally distributed data). Frequency counts and percentages of subjects within each category will be provided for categorical data. Visual inspection of box plots of number of quit attempts and number of cigarettes smoked daily (if still smokers) will be used to identify possible outliers to be excluded in sensitivity analyses.

#### Primary analyses

The primary analyses will assume that missing outcome data are missing at random and, therefore, will be performed on complete cases only.

The binary outcomes of self-reported prolonged abstinence, 4-week prevalence of smoking abstinence and 7-day point prevalence of smoking abstinence will be analysed by logistic regression and results presented as odds ratio (95% CI). Number of quit attempts and number of uses of other smoking cessation services will be analysed by negative binomial regression and results presented as ratio of means (95% CI). Numbers of cigarettes smoked weekly will be analysed by logarithmic transformation and linear regression and results presented as ratio of geometric means (95% CI).

All regression analyses will be adjusted for by the following baseline variables: gender, years of smoking, average number of cigarettes smoked weekly, severity of dependence as measured by Fagerström’s Nicotine Dependence Scale and amount of ‘*snus*’ used at baseline.

Effect modification analyses will be performed for the two primary outcomes and the following potential effect modifiers measured at baseline: gender, average number of cigarettes smoked weekly, amount of ‘*snus*’ used weekly, and severity of dependence as measured by Fagerström’s Nicotine Dependence Scale. Each effect modification will be assessed by adding the appropriate interaction term to the adjusted regression model. Consideration for adjustment for multiplicity of comparisons will be discussed. All tests will be performed 2-sided with a 5% level of significance.

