## Methods/design

### Design

This is a 2-arm RCT study in which participants are randomised to an intervention (group 1) or a waiting list (group 2). In Additional file 1, the recommended items included in the reporting of the RCT are listed. After the 12-week intervention all participants in both groups will be asked to complete a follow-up questionnaire after which the control group will be given access to the intervention. The study will be performed simultaneously at all universities and colleges in Sweden.

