### Outcome evaluation

The baseline questionnaire contains 19 questions about sociodemographic data and smoking habits. The participants will be asked to state their age, gender, marital status and years of smoking and, if using Swedish snuff (‘*snus*’), how much per day. Then follows the 6 questions of Fagerström’s Nicotine Dependence Scale and a question on how important it is for the participants to quit smoking with response option on a scale from 1 to 10, where 1 stands for not important at all and 10 very important. All participants will be asked if they ever have tried to stop smoking before (and if so how many times); if they ever have tried nicotine replacement (if so how many times); if they have been prescribed drugs for smoking cessation, and if they have received professional counselling or if they have called the national quit smoking help-line.

After 4 months, a link to an electronic follow-up questionnaire will be Emailed to all participants. Initially, 2 reminders 1 week apart will be sent to non-responders. In order to minimise attrition those participants still not responding will receive additional Email reminders every second day for 6 days (that is 3 Emails). If still not responding, the non-responders will receive a SMS every second day for 6 days (that is 3 SMS) with only 2 questions to answer, to capture the 2 primary outcome measures. Lastly, those still not responding will be phoned with a maximum of 10 calls per participant. Also, in the invitation to answer the follow-up questionnaire the participants will be told that they are offered the opportunity to be part of a draw for a number of iPads (Apple Inc., Cupertino, CA, USA) after having answered the follow-up questionnaire.

Outcome measures are as follows:

*Primary outcome measures*:Self-reported prolonged abstinence (defined as having not smoked more than 5 cigarettes in the last 8 weeks).Self-reported 4-week point prevalence of smoking abstinence (not having smoked a single cigarette).

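### The two count outcomes have no end date, so each participant's counting period depends on when they answer; closing both counts at a fixed date removes a small, conditional risk of bias

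*Protocol article*

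**What the plan says.** Outcome evaluation defines the first count as "Mean number of quit attempts since taking part in the study". The second counts uses of medication, nicotine replacement, counselling, "calling the help-line or any other help) since first invitation to the study". Each definition fixes a start and no end. The abstinence outcomes, by contrast, have closed look-backs of 8 weeks, 4 weeks and 7 days.

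The same section spreads the answers over time. It begins: "After 4 months, a link to an electronic follow-up questionnaire will be Emailed to all participants". Then: "Initially, 2 reminders 1 week apart will be sent to non-responders". After that, "those participants still not responding will receive additional Email reminders every second day for 6 days (that is 3 Emails"). A text-message stage follows that asks only the two primary outcomes, and then up to 10 calls whose content is not stated.

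Primary analyses sets the model: "Number of quit attempts and number of uses of other smoking cessation services will be analysed by negative binomial regression and results presented as ratio", where the quantities compared are means, with a 95% confidence interval. On covariates it says "All regression analyses will be adjusted for by the following baseline variables: gender, years of smoking, average number of cigarettes smoked weekly", followed by the Fagerström score and snus use. Neither an exposure term nor a response-time variable is mentioned. Sensitivity analyses and Discussion do use response timing, but for missing-data and data-quality questions and not in the count models.

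**The concern.** A count that stays open until the questionnaire is answered gives a late responder more time in which to report events. A ratio of means treats all participants as if they had been counted over the same period. If one arm answered later on average, part of any difference in means would reflect counting time and not the intervention.

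Participants know their arm, so different response speeds are possible. At stake are the estimates and the type I error for hypotheses 4 and 5 (quit attempts and use of other services). The two primary outcomes use fixed look-backs and do not have this problem.

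**Working it through.** **Inputs from the article.** Follow-up at 4 months; two reminders one week apart; three further Emails over 6 days; 474 analysed per group.

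**Assumptions, not in the article.** 4 months = 122 days; mean response on day 5 after the link in the faster arm; mean count 1 to 3; negative binomial dispersion 0.5 to 1; a range of between-arm differences in mean response time.

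**The plan's own figure.** The article gives no figure for the count outcomes. Its sample size, used here only for the standard error, reproduces. For 5% versus 10%, two-sided 0.05 and 80% power, n is 435 per group uncorrected and 474 with the continuity correction; 474/0.7 = 677.1.

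**Step 1: spread between individuals.** The weekly reminders fall on days 7 and 14. If the extra Emails follow at once, the last falls by day 14 + 6 = 20. If another week passes first, it falls by day 14 + 7 + 6 = 27. The counting period relative to a day-0 responder is (122 + 20)/122 = 1.16 to (122 + 27)/122 = 1.22. The text-message stage yields no counts. The phone stage would extend the spread only if the calls ask the count items.

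**Step 2: bias in the ratio of means.** With a true ratio of 1 and a constant event rate, the expected ratio is the ratio of mean counting times. For a difference of d days this is (127 + d)/127, where 127 = 122 + 5. One day is worth 1/127 = 0.8%. For service use the base is longer, because counting starts before randomisation, so the effect per day is a little smaller.

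**Step 3: effect on the test.** SE of the log ratio = sqrt(2(1/mean + dispersion)/474). Actual size = P(|Z + ln(ratio)/SE| > 1.96).

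| Difference in mean response time | Ratio of means when the true ratio is 1 | Size of nominal 5% test |
|---|---|---|
| 0 days | 1.00 | 5% |
| 2 days | 129/127 = 1.016 | 5.3 to 5.8% |
| 5 days | 132/127 = 1.039 | 7.0 to 10.0% |
| 10 days | 137/127 = 1.079 | 13.1 to 24.8% |

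The ranges cover means of 1 to 3 and dispersions of 0.5 to 1. As one case, mean 1.5 and dispersion 1 give SE = sqrt(2 × 1.667/474) = 0.084 and a size of 7.5% at 5 days.

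**Step 4: simulation.** In 400 simulated trials with constant rates and a mean difference of 4.1 days, the ratio averaged 1.035 without an offset, with 6.0% rejections. With a log-exposure offset it averaged 1.003, with 4.0% rejections. The Monte Carlo standard error is sqrt(0.05 × 0.95/400) = 1.1 percentage points, so neither rejection rate can be told from 5%. The shift in the ratio agrees with Step 2.

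**Step 5: early clustering.** Suppose events after month 4 occur at half the average rate (assumed). A 5-day difference then adds 2.5 day-equivalents: 129.5/127 = 1.02, with a size of about 5.6% at SE 0.084. An offset would divide this by 1.039, giving 1.020/1.039 = 0.98, a bias of similar size in the other direction.

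**The case against.** The strongest reply is that the condition for bias is not shown. The article has no data on response speed by arm. The iPad draw, the fortnightly thank-you messages and the two-week notice of follow-up are the same in both groups. This stands: with equal mean response times there is no bias.

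A reader might infer that controls will answer sooner, which would inflate the ratio in the direction of hypotheses 4 and 5. Under Design, "all participants in both groups will be asked to complete a follow-up questionnaire after which the control group will be given access to the intervention", which could reward an early answer. But under Randomisation and other study procedures, controls are told only that access comes after 4 months, which is a date and not a return for answering. The direction therefore cannot be settled from the article.

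A reader might also take the 16 to 22% as the size of the bias. It compares two individuals at opposite ends of the Email schedule, whereas bias depends on the difference between arm means. Nor is it established that late responders have more events. All participants must be willing to set a quit date within 4 weeks, so attempts may well cluster early.

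Finally, the article may condense the plan, and the questionnaire wording is not shown. That carries some weight for the missing offset. It carries less for the outcome definitions, which state a start without an end, in an article whose Data analysis section says that the prespecified plan is described there.

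**Conclusion.** The point holds in a limited form. Both count outcomes are open-ended as defined, and the counting period varies by design with the time of response. Bias in the ratio of means is conditional on the arms differing in mean response time. It is at most about 0.8% per day of difference under a constant event rate and a base of 127 days, so about 1.02 at 2 days and 1.04 at 5 days. It is less if attempts cluster near the quit date. Differences of 10 days would matter more, but nothing in the article suggests them.

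The stronger reading, that the planned analysis is biased towards the intervention and needs an offset in its main model, is not supported. Two secondary outcomes are affected and no primary outcome is. This is a cheap improvement to the outcome definitions, not a flaw that undermines the trial.

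A related inconsistency adds to the case for a fixed end. Design places control access after the follow-up questionnaire, while Randomisation and other study procedures gives it as after 4 months. If access came at a fixed date, late control answers could include events after access. The two sections must be reconciled.

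**What to change.** - Define both counts as ending at a fixed date per participant, the date of the first 4-month follow-up Email. State this in the outcome definition and in the question wording.
- Tabulate response time by arm, so that a reader can see whether counting time could have differed.
- Use a log-exposure offset at most as a sensitivity analysis. Measure exposure from the start of each count: study entry for quit attempts, first invitation for service use. The offset assumes even accrual and uses a post-randomisation variable that the protocol itself suspects may be related to outcome.
- Reconcile the sections on when controls gain access.

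The cost is a change of wording and one table. At the protocol date, 7 November 2014, recruitment was still open and the 4-month follow-up had not begun, so the wording could still be changed. The downside is slightly harder recall for late responders, who must report up to a date some weeks past.
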